### Blinding

The participants, the researchers delivering the intervention, those performing the assessments, and the statistician will be blind to group allocation until after the data analysis. To ensure proper blinding, participants will receive codes and will be separated from the allocation process by a different investigator. The researchers responsible for applying the intervention and the outcome assessors will not know the allocation of the participants. In addition, for the blinding of the experimenter, the device to be used has a “study” mode, in which a code is inserted for each participant, so the device (DS-Stimulator Mobile, neuroConn^®^, Ilmenau, Germany) recognises and programmes the settings (active or sham). Further details about settings used in both active and sham interventions are presented in section tDCS Intervention.

### Assessment Scales and Tasks

We will use two classification systems to characterise both groups, five assessments to characterise participants and to measure improvement, and one physiological assessment; and one enjoyment scale, four visual assessments, one cognitive assessment, and two VR tasks (reaction time and coincident timing) for motor performance.

### Classification Systems for Group Characterisation

#### Manual Ability Classification System (MACS) for Children With CP

The MACS describes how children with CP use their hands to manipulate objects in daily activities, and is used for children and adolescents aged 4 to 18 years (34, 35).

The MACS has five levels. They are based on a child's ability to initiate the manipulation of age-appropriate objects alone and on the need for assistance or adaptation to perform manual activities in daily life. Levels are determined by a parent or caregiver who regularly observes the child's day-to-day functions in collaboration with a healthcare professional.

Children who are able to manipulate objects easily with maximum limitations to perform manual tasks that require speed and accuracy are classified regardless of their age as level I, and those who handle objects of lower quality and speed are classified as level II. Children at level III manipulate objects with difficulty and need help or an adapted activity, and those at level IV require continuous support and assistance and/or adapted equipment adapted to partially perform the activity. Finally, children at level V are severely compromised in manual skills and need full assistance. Given the difficulties associated with this level, it will be an excluded item in our study.

#### Gross Motor Function Classification System (GMFCS)

GMFCS is a reliable and valid standard classification system for measuring the functional abilities of children with CP (36). It describes self-initiated movement and the use of assistive devices (walkers, crutches, canes, wheelchairs and so on) for mobility during an individual's daily activities.

It uses locomotion as a key assessment and analyses the individual at five levels of locomotor performance, separated by age range from 0 to 18 years (37, 38). Thus, an individual classified as GMFCS I is able to walk without limitations. A child classified as level II may walk with limitations, where a GMFCS II operation may result in the use of wheeled mobility over long distances. A GMFCS III-graded child can usually walk with a portable mobility device indoors, but uses wheeled mobility in the community over longer distances. A GMFCS IV-rated individual may sit supported, but their own mobility is limited and they are often carried in a manual wheelchair or use motorised mobility. Children classified as GMFCS V have more severe limitations with head and trunk control, and self-mobility is only possible with an electric wheelchair (37). Considering the difficulties that are associated with level V, it will be an excluded item for our study.

### Assessments to Characterise Participants and Measure Improvement

#### Pediatric Evaluation of Disability Inventory (PEDI)

The PEDI is a standardised instrument consisting of a structured interview with the caregiver, capable of documenting the functional performance of children between 6 months and 7 years old in their daily life activities (39, 40).

This test covers three domains: self-care, mobility, and social function. The self-care scale covers food, personal hygiene, toilet use, clothing, and toilet control. The functional items of mobility provide information about transfers, walking indoors and outdoors, and use of stairs. The social function dimension reflects issues related to communication, problem solving, interaction with colleagues, amongst others.

Total scores are calculated for each scale in each domain, where each item receives a score of 0 (the child is unable to perform the activity) or 1 (the activity is part of the child's repertoire), and the sum of the items generates the score for each domain. Studies have shown that the PEDI test is valid and sufficiently reliable to be applied to children with CP in Brazil (40, 41).

#### ABILHAND-Kids

ABILHAND-Kids is a questionnaire about manual ability in self-care activities in children with upper limb involvement based on their parents' perception (42, 43).

The scale consists of 21 mainly bimanual items classified by parents as impossible, difficult, easy to complete, or unknown, defining a one-dimensional measure of manual skill in children with CP.

Scores are significantly related to school education, CP type, and gross motor function, but not to age, sex, or laterality (42, 44).

Finally, ABILHAND-Kids measures are significantly related to GMFCS levels; a higher manual skill is related to a higher gross motor function. A similar relationship between bimanual fine motor function and GMFCS levels has been found previously (45).

#### ACTIVLIM-CP

The ACTIVLIM-CP is a questionnaire for parents that measures the performance of global activity in daily activities. It has been validated for children with CP (46–48).

It includes 43 items of activities of daily living related to self-care, mobility, and domestic life, and represents a valid and reliable measure of the performance of global activity. In addition, the ACTIVLIM-CP was built based on parents' perception. They are asked to estimate the ease or difficulty their children have in performing each activity, by rating this on a three-level scale: impossible (the child is unable to perform the activity without using any other help), difficult (the child is able to perform the activity without any help, but experiences some difficulty), or easy (the child is able to perform the activity without any help and experiences no difficulty).

### Physiological Assessment (HRV)

We will use HRV to analyse autonomic nervous systems before, during, and after the intervention recovery. The analysis will follow the guidelines of the Task Force of the European Society of Cardiology and the North American Society of Pacing and Electrophysiology (49). The strap (for data collection) will be positioned on the participant's chest, and the Polar V800 (Polar Electro, Finland) heart rate receiver will be positioned next to it. HRV will be recorded after the initial assessments at rest for 10 min and during VR combined with tDCS training for 20 min. For analysis of HRV data at rest 1,000 consecutive resting rate (RR) intervals will be used, and during the tasks 256 consecutive RR intervals will be used.

Heart rate will be recorded beat by beat throughout the protocol by the Polar V800 heart rate receiver and RR intervals recorded by the monitor will be transferred to the Polar ProTrainer program, which allows HR visualisation and cardiac period extraction in the “txt.” file format.

Moderate digital filtering will be performed in the program itself, complemented with manual filtering performed in Excel software to eliminate premature ectopic beats and artefacts, and only series with more than 95% sinus beats will be included in the study (50).

HRV analysis will be performed using linear (time and frequency domain) and non-linear methods that will be analysed using Kubios HRV^®^ software (Kubios HRV v.1.1 for Windows, Biomedical Signal Analysis Group, Department of Applied Physics, University of Kuopio, Finland).

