## Assessment Protocol

The assessment protocol will have the following sequence: the assessment scales will be undertaken with the participants' parents in a separate room (PEDI, Abilhand-Kids, and *ACTIVLIM-CP*), and GMFCS and MACS will be carried out by observacional analysis of their abilities. Also, cognitive (WISC-IV) and visual assessments (*Titmus Test and Ishihara Test)* will be made by a psychologist and a psychometrist, respectively.

Then, for the VR assessment, the coincident timing task will be carried out with a short-term motor learning protocol as used by Monteiro et al. (17), with 20 repetitions for acquisition. After 15 min of no contact with the task, the participants will perform five repetitions of the same task (for retention analysis), and five more repetitions with a speed increase (for transfer of performance analysis).

The reaction time task will be carried out with two attempts of adaptation and 10 attempts for analysis, as used by Crocetta et al. (71).

The HRV will be assessed by 20 min of rest seated in a comfortable chair or their own wheelchair, as used by Alvarez et al. (72).

The assessment part of the protocol will take around 1 h and 30 min in total (inferential analysis method follows in the item “Data analysis”).

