### Assessments for Secondary Outcome

In addition to the motor tests, the HRV analysis will be verified throughout the intervention. Some studies point to ANS alteration, with a reduction in HRV in individuals with CP (77, 78). HRV represents the autonomic function, and short-term HRV measurement has been used to evaluate sympathetic and parasympathetic heart rate modulation. Therefore, because of the ease of evaluation (non-invasively, through a chest strip) and because of its high clinical relevance, it is important to evaluate HRV before and during the intervention with tDCS and VR, since some studies indicate improvement of the autonomic balance after VR tasks in individuals with Duchenne muscular dystrophy (72) and post-stroke (79). In the case of CP, some studies had identified low HRV in foetuses that would later be given a CP diagnosis (80), at rest and during postural change (81), and submaximal tests (78). Low HRV is often an indicator of abnormal and insufficient ANS adaptation, which may indicate the presence of physiological malfunction in the individual (50) and is associated with an increased risk of cardiac events (6).

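### Resting HRV is set at 10 min in one section and 20 min in another, and 10 min cannot supply the 1,000 resting RR intervals unless mean heart rate is at least 100 bpm

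*Protocol article*

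**What the plan says.** The protocol article describes the resting HRV recording in two places.

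- Physiological Assessment (HRV): "HRV will be recorded after the initial assessments at rest for 10 min and during VR combined with tDCS training for 20 min".
- Assessment Protocol: "The HRV will be assessed by 20 min of rest seated in a comfortable chair or their own wheelchair".

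The first of these sections also fixes the analysed segments. For rest it states: "For analysis of HRV data at rest 1,000 consecutive resting rate (RR) intervals will be used". Task recordings are analysed in a shorter segment of 256 intervals. The section sets one quality rule, "only series with more than 95% sinus beats will be included in the study", and describes the indices only by family: "HRV analysis will be performed using linear (time and frequency domain) and non-linear methods".

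On the intended use, Assessments for Secondary Outcome states that "it is important to evaluate HRV before and during the intervention with tDCS and VR". The Physiological Assessment section and the Discussion likewise speak of HRV before, during and after. Table 1 lists HRV improvement as the key secondary outcome. The Statistical Analysis section plans repeated-measures or Friedman analyses of HRV within groups, and ties the repeated measures to the evaluations and follow-up.

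**The concern.** Two resting durations are given, and the required interval count looks feasible under only one of them for children with ordinary resting rates. If the 10-min text governs, a record can fall short of 1,000 intervals. The team must then either treat the requirement as unmet or analyse whatever length is available, in which case the window length varies with heart rate. The plan does not choose between these, so the resting dataset for the key secondary outcome is not defined.

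The resting segment is also about four times as long as the task segment. RR series contain slow components, so some variability indices grow with record length. A direct comparison of rest with task could then show a fall in variability that comes from the window alone.

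**Working it through.** **Inputs.** From the protocol: resting record of 10 min or 20 min; 1,000 consecutive RR intervals at rest; 256 during tasks; more than 95% sinus beats. Assumptions, because the protocol gives no values: resting heart rate of 70-90 bpm, with 100 bpm shown as the threshold; loss of 5% of beats to filtering as an illustration; and the spectral shape used in step 4.

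**1. Heart rate needed for 1,000 intervals.** Required rate = 1,000 / minutes.

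- 10 min: 1,000 / 10 = 100 bpm. With 5% of beats removed: 1,000 / 0.95 / 10 = 105.3 bpm.
- 20 min: 1,000 / 20 = 50 bpm. With 5% removed: 1,000 / 0.95 / 20 = 52.6 bpm.

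**2. Intervals available.** Intervals = heart rate x minutes.

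| Mean heart rate (assumed) | In 10 min | In 20 min | Time needed for 1,000 |
|---|---|---|---|
| 70 bpm | 700 | 1,400 | 14.3 min |
| 80 bpm | 800 | 1,600 | 12.5 min |
| 90 bpm | 900 | 1,800 | 11.1 min |
| 100 bpm | 1,000 | 2,000 | 10.0 min |

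The protocol's pairing of 10 min with 1,000 intervals is therefore reproduced only at 100 bpm or above, before any beat is lost.

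**3. Ratio of window lengths.** 1,000 / 256 = 3.9 at equal heart rate.

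**4. Effect of window length with no true change.** For each setting, 3,000 stationary series with spectrum 1/f^beta were simulated. The mean SD of the RR intervals (SDNN) and the mean root mean square of successive differences (RMSSD) in the first 256 points were divided by the same means over the full 1,000 points.

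| beta (assumed) | SDNN, 256 / 1,000 | RMSSD, 256 / 1,000 |
|---|---|---|
| 0 (white noise) | 1.00 | 1.00 |
| 0.5 | 0.99 | 1.00 |
| 1.0 | 0.89 | 1.00 |
| 1.2 | 0.83 | 1.00 |

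The spurious fall in SDNN runs from 0% to 17% (1 - 0.83). RMSSD does not move.

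**The case against.** **The two durations may describe different things.** Ten minutes of recording could sit inside 20 min of seated rest. The protocol does not say so, and this reading confirms the 10-min recording, so the 100 bpm threshold stays.

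**The monitor records every beat for the whole session.** This is true, but it does not lengthen the rest period. If rest really lasts 20 min, the longer record is available and the shortfall disappears. That is the Assessment Protocol version, and the other section then needs correcting.

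**No rest-versus-task test is specified.** This largely stands. The Statistical Analysis section attaches the repeated measures to evaluations and follow-up, which reads as assessment occasions. The repeated references to HRV before and during the intervention make a direct comparison plausible, but it is inferred. Different segment lengths are a fault only if the two conditions are contrasted.

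**The size of the window effect is assumed.** This also stands. The protocol names no single index and supports no particular spectral exponent, so the number of affected indices is unknown and the 17% belongs to one chosen exponent.

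A reader might also infer that children with slower resting hearts would be dropped, selecting the sample on autonomic state. The protocol does not support this: its only stated HRV exclusion is the sinus-beat rule, and no rule discards a short record.

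**Conclusion.** The contradiction between 10 and 20 min is plain in the text. The incompatibility of 10 min with 1,000 intervals below 100 bpm is exact arithmetic. How many children would fall short cannot be stated, because resting heart rates are not given; the 700-900 intervals rest on the assumed 70-90 bpm. The plan leaves open whether a short record fails the rule or is analysed at its own length.

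The window-length point holds only conditionally: for length-dependent indices such as SDNN and total power, and only if rest and task are compared directly. It would be wrong to conclude that the unequal windows bias the treatment effect. Active and sham at the same stage use the same segment length, so that contrast is not biased by the mismatch. It would equally be wrong to conclude that every rest-to-task comparison is biased, since RMSSD-type indices are unaffected in expectation. The point should be corrected because it concerns the key secondary outcome, but it does not threaten the main active-versus-sham question.

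**What to change.** 1. State one resting duration in both sections, with an interval count it can supply: either 20 min with 1,000 intervals, or 10 min with a smaller count. If recordings already exist, the text should follow the duration actually used, since a 10-min record cannot be lengthened afterwards.
2. State what is done with a record that falls short of the count.
3. For any direct rest-versus-task comparison, use equal windows, for example 256 consecutive intervals at a fixed position in each recording. This works with either resting duration: 256 / 10 = 25.6 bpm is enough for a 10-min record. Keep the longer window for rest-versus-rest comparisons.

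The cost is a few sentences and some re-windowing of recordings. Resting indices from 256 intervals will be somewhat noisier in the rest-versus-task comparison.

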### Enjoyment Scale

An enjoyment scale using smiley faces (0 is “not fun at all;” 1 is “boring;” 2 is “a bit of fun;” 3 is “fun;” and 4 is “great fun”) will be applied after the end of the game sequences, since the motivation may be related to the motor proficiency level.

This scale was developed by Jelsma et al. (51) to evaluate how children feel when interacting with proposed non-immersive VR games. It was used in other studies using different games (52, 53).

In this study, the scale will be applied in the first and last days of the protocol to verify the children's level of satisfaction with the games presented.

### Visual Assessments

For visual evaluation the following tests will be used: the Ishirara Test and the Titmus Test.

#### Ishihara Test

The Ishihara Test (chromatic vision—Ishirara pseudoisochromatic slides) is the best known and most widely used in the world for green and red colour perception or colour blindness. It was originally created to diagnose congenital colour vision deficiencies, but it has also been shown to be effective in identifying acquired colour deficiencies (54, 55). Its application is based on the analysis of planks formed by coloured circles, with two or three shades and different sizes on a background of similar colour and structure, in which a number or maze appears in a certain colour, which should be identified by the possible bearer of the disability (56).

The boards can be classified into: demonstration boards—visible to all observers in which the figure is presented with a significant contrast brightness against the background, making chromatic sensitivity not necessary for a correct answer; and masking boards—only individuals with normal vision can see the picture in which the object is close in colour to the background (54, 56).

#### Titmus Test

The Titmus Test is a test used to assess stereoscopic vision or depth perception (the “3D view”) that is given by both eyes together and based on the principle of polarisation. It is composed of a two-sided book, and on each side are arranged figures that are projected in duplicate and horizontally disparate from each other (57).

With the use of polarised glasses, and the book positioned between 30 and 40 cm from the eyes, the participant is instructed to indicate the figures they perceive in “relief” (three-dimensional). This perception of three-dimensionality is image disparity, and is measured in arc seconds (57–59).

Quantitatively the steroscopic acuity in this test ranges from 3,000 to 40 seconds of arc, and the level of image disparity decreases as the participant is able to identify them. Therefore, the lower the numerical value in arc seconds, the greater the stereoscopic acuity (57, 59).

### Cognitive Assessment

The Wechsler Intelligence Scale for Children (WISC-IV) was developed to assess intelligence in children and adolescents. Because it assesses different intellectual aspects, WISC-IV can be used in different situations, such as psychoeducational, clinical and neuropsychological assessment, diagnosis of neurodevelopmental disorders, and psychiatric disorders (60, 61), and is indicated for the evaluation of subjects between 6 and 16 years old (62, 63).

The WISC-IV is composed of 15 subtests divided into four indices: verbal comprehension, perceptual organisation, working memory, and processing speed (61). The Intelligence Quotient is considered a global cognitive functioning index and traditionally used as a crucial measure in case-control studies in neurodevelopmental disorders (64).

### VR Task for Assessment

We will use two VR tasks to assess the participants' capacity and improvement with intervention. The tasks will be used as assessment at three points: initial assessment (D0); assessment after 5 sessions (D5); and final assessment (D11).

The assessment tasks are presented below:

#### Coincident Timing

Coincident timing is defined as the perceptual motor ability to perform a motor response in synchrony with the arrival of an external object at a given point (65, 66). This task will use non-immersive virtual coincident timing software, which displays on the computer screen (of a 15' computer) 10 (3D) spheres that light up (in red) in sequence until the last sphere—the target—is reached. The participant must rest his/her hand next to the keyboard of the computer and then press the space key at exactly the moment when the last (target) sphere lights up. The software provides immediate feedback on the success or otherwise of the task by means of different previously demonstrated sounds and colours [for more details, see (8, 17, 67, 68)]. If the participant anticipates or delays the timing of the stimulus, a red light will appear around the feedback; if he/she hits the target, a green light will appear (Figure 3).

**Figure 3 F3:**
[figure not shown]
Representative design of the accomplishment of the coincident timing task. **(A)** Demonstration of error performed by the participant on each attempt (red light–unsuccessful). **(B)** Demonstration of hit performed by the participant on each attempt (green light–successful). **(C)** Demonstration of the movement on the space bar on keyboard to perform the task. Main image is about an example of the initial position of the participant.

The magnitude and direction of error of each participant in anticipating or delaying the arrival of the light is recorded by the software in milliseconds. The object is to evaluate the time difference between the participant's response and the arrival of the object at the target location (accuracy) and his/her global temporal precision and therefore his/her coincidence–anticipation ability (8, 17, 67, 69, 70).

The software is programmed to provide a unique username for each participant and the following data are stored: participant name, date of birth, sex, and the researcher's name.

